# Study design and rationale of the ‘Balloon-Expandable Cobalt Chromium SCUBA Stent versus Self-Expandable COMPLETE-SE Nitinol Stent for the Atherosclerotic ILIAC Arterial Disease (SENS-ILIAC Trial) Trial’: study protocol for a randomized controlled trial

**DOI:** 10.1186/s13063-016-1435-9

**Published:** 2016-06-25

## Abstract

**Background:**

The self-expandable COMPLETE™ stent (Medtronic) has greater elasticity, allowing it to regain its shape after the compression force reduces, and has higher trackability, thus is easier to maneuver through tortuous vessels, whereas the balloon-expandable SCUBA™ stent (Medtronic) has higher radial stiffness and can afford more accurate placement without geographic miss, which is important in aortoiliac bifurcation lesions. To date, there have been no randomized control trials comparing efficacy and safety between the self-expanding stent and balloon-expandable stent in advanced atherosclerotic iliac artery disease.

**Methods/design:**

The purpose of our study is to examine primary patency (efficacy) and incidence of stent fracture and geographic miss (safety) between two different major representative stents, the self-expanding nitinol stent (COMPLETE-SE™) and the balloon-expanding cobalt-chromium stent (SCUBA™), in stenotic or occlusive iliac arterial lesions. This trial is designed as a prospective, randomized, multicenter trial to demonstrate a noninferiority of SCUBA™ stent to COMPLETE-SE™ stent following balloon angioplasty in iliac arterial lesions, and a total of 280 patients will be enrolled. The primary end point of this study is the rate of primary patency in the treated segment at 12 months after intervention as determined by catheter angiography, computed tomography angiography, or duplex ultrasound.

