#### Sample size calculation

Although patency definitions varied across trials, 1-year patency rates in aortoiliac lesions were approximately 90 % on average from previous studies including CRISP-US and MELODIE [22, 23]. In the case of the SCUBA™ stent, the 9-month patency rate for the SCUBA™ stent was 99.2 % in the ACTIVE study - a prospective, multicenter, single-arm study that defines the midterm efficacy of a next-generation cobalt-chromium iliac stent for the treatment of de novo and restenotic lesions in iliac arteries [25]. However, a different definition - a ratio of <2.4 between the duplex peak systolic velocity in the treated vessel segment and the reference systolic velocity - was used, unlike the more common definition. There are limited data on the 1-year primary patency rate of the SCUBA™ stent. Based on the MELODIE trial [23], and the European multicenter iliac stent trial [26], the 1-year primary patency of the SCUBA™ stent was estimated to be 88 %, and the COMPLETE-SE™ stent was estimated to be 94.7 % in the CRISP-US trial. Therefore, the self-expandable COMPLETE-SE™ stent group will be the control group, and the balloon-expandable SCUBA™ stent group will be the experimental group.

Patency rate will be defined as absence of occlusion and absence of >50 % stenosis in the treated segment by quantitative coronary angiography (QCA) or if invasive angiography is not performed, PSVR ≤2.5 when evaluated with duplex ultrasound. On the basis of previous studies [22, 23], we hypothesize that the expected patency rate after stent deployment at 1 year would be 90 % for the self-expandable stent group, and 88 % for the balloon-expandable stent group, respectively. The predetermined noninferiority margin δ is a 10 % difference between treatment groups. There was clinical consensus that this noninferiority margin would be acceptable if safety is maintained and patients are treated more easily, regardless of stent classification. The power analysis is based on a noninferiority principle. The statistical significance level is 2.5 % at one side, the power of the test is set as 80 %, and the randomization ratio is set as 1:1. The test for proportion and the chi-square method will be used. Using standard sample size formula, it was calculated that 120 patients per group are needed for a total of 288 patients, after accounting for a 20 % dropout rate.

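### Two enrolment totals are given, 280 and 288, and neither leaves the stated 120 evaluable patients per group after 20% dropout; that takes 300

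*Protocol article*

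**What the plan says.** The Methods/design paragraph of the abstract states that "a total of 280 patients will be enrolled". At 1:1 allocation that is 140 per group.

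The section Sample size calculation states that "120 patients per group are needed for a total of 288 patients", "after accounting for a 20 % dropout rate". The same section says "the randomization ratio is set as 1:1" and gives the design inputs: "The statistical significance level is 2.5 % at one side", 80% power, a noninferiority margin of 10 percentage points, and expected 12-month patency that "would be 90 % for the self-expandable stent group" and "88 % for the balloon-expandable stent group".

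The Statistical analysis section says that missing data on the major end points will be left out of the analysis. The article does not explain the difference between 280 and 288, and the abstract does not present its figure as approximate.

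**The concern.** There are two faults in one short calculation. First, the same trial has two recruitment targets, so the point at which enrolment stops is not fixed. The Trial status section says recruitment is under way, so this matters in practice.

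Second, 288 looks like 240 raised by 20%. A 20% dropout rate applies to the patients enrolled, not to the patients needed at the end. Multiplying the final number by 1.2 therefore falls short of replacing the losses.

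The plan has no cushion for the shortfall. A patient without a 12-month patency result leaves the denominator. The 12-month imaging is only recommended, so some missing results are foreseeable. Noninferiority also requires consistent intention-to-treat and per-protocol conclusions, and the per-protocol set cannot be larger than the set of all assigned patients.

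**Working it through.** **Inputs** (all from Sample size calculation, except the abstract's 280)

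- Needed per group: 120, so 240 in total at 1:1
- Dropout: 20%
- Stated totals: 288 (Sample size calculation) and 280 (abstract)
- Patency 90% (control) and 88% (experimental), margin 10 points, one-sided 2.5%, power 80%

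**Step 1. Reproduce the stated total.**
240 × (1 + 0.20) = 288. This matches exactly, so multiplication is the likely route, although the article says only that a standard formula was used. The abstract's 280 comes from neither multiplication (288) nor division (300).

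**Step 2. Apply the dropout rate to those enrolled.**
If a fraction d of N enrolled patients is lost, N × (1 − d) remain. To have 240 remaining, N = 240 / (1 − 0.20) = 300, or 150 per group.

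**Step 3. What each total delivers.**

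| Enrolled | After 20% loss | Per group | Short of 240 by | Dropout at which 240 remain |
|---|---|---|---|---|
| 280 | 280 × 0.8 = 224 | 112 | 16 | 1 − 240/280 = 14.3% |
| 288 | 288 × 0.8 = 230.4 | 115.2 | 9.6 | 1 − 240/288 = 16.7% |
| 300 | 300 × 0.8 = 240 | 120 | 0 | 20% |

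**Step 4. Effect on power at the plan's assumptions.**
Unpooled normal approximation: power = Φ[(0.10 − 0.02) / SE − 1.96], with SE = √[(0.90 × 0.10 + 0.88 × 0.12) / n] = √(0.1956 / n).

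| n per group | SE | 0.08 / SE | Power |
|---|---|---|---|
| 112 | 0.0418 | 1.914 | 48% |
| 115 | 0.0412 | 1.940 | 49% |
| 120 | 0.0404 | 1.981 | 51% |
| 240 | 0.0285 | 2.802 | 80% |

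The dropout error accounts for the drop from 51% to 49% or 48%. The rest of the gap to 80% comes from the figure of 120 itself.

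**Step 5. Does the error survive correction of the 120?**
From the stated inputs, n = (1.96 + 0.8416)² × 0.1956 / 0.08² = 240 per group. Pooled variance gives 241, Farrington-Manning 255 and a continuity correction 265. With 240 per group:

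- Multiplying: 480 × 1.2 = 576, and 576 × 0.8 / 2 = 230.4 per group, with power about 78%.
- Dividing: 480 / 0.8 = 600, and 600 × 0.8 / 2 = 240 per group, with power 80%.

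So the dropout step is wrong whichever per-group number is used.

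**The case against.** The strongest objection concerns weight. Multiplying by 1 + d is a common shortcut, the 20% is an unsourced planning guess, and 288 still covers 16.7% dropout. The gap to 300 is 12 patients, or 4%. A reader would probably take the sample size section, where the total is derived, as governing over the abstract, and the two differ by only 8 patients. This stands as a limit on size. It does not rescue the statement, because the plan says 20% is covered and it is not, and the shortcut cannot explain 280.

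A second objection is that 300 follows only if 120 per group is accepted, and the plan's own inputs do not support 120. A reader could think that moving to 300 repairs the design, when power would still be about 51%. This is right, and the 300 must be read as conditional. For the same reason the 48% and 49% should not be charged to the dropout error: at 120 per group the power is already about 51%.

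A third is that the multiplication is inferred from an exact match rather than stated. That is also fair, but the shortfall in Step 3 does not depend on how 288 was reached.

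**Conclusion.** The concern holds. The article gives two unreconciled enrolment totals, and neither leaves 120 evaluable patients per group at its own 20% dropout rate. Taking 120 per group as given, the consistent total is 300: 12 more than the sample size section and 20 more than the abstract. At 20% dropout the evaluable shortfall is about 10 patients with 288 and 16 with 280. The direct cost is 2 to 3 percentage points of power.

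This assumes that dropout means patients without a primary outcome, which fits the plan to exclude missing primary data, and that losses are equal in the two groups. The power figures also assume the stated 90% and 88% patency and the unpooled normal approximation. The per-group figure of 120 is a separate and larger error, and correcting the dropout step does not cure it.

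**What to change.** 1. Recompute the per-group number from the stated rates, margin, significance level and power. Those inputs give 240, not 120.
2. Divide the result by (1 − 0.20). This gives 300 in total if 120 per group is kept and 600 if 240 is adopted.
3. State that one total in both the abstract and the sample size section, with the evaluable number per group it is meant to yield and the power at that number.

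If the sponsor keeps 288, the text should say that it yields about 115 evaluable per group at 20% dropout, or that it covers 16.7% dropout for 120 per group. Either way it should give the power of about 49% or 51% at the stated assumptions.

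Restating the allowance or the evaluable number is a change of wording only. Keeping both 120 per group and 20% dropout costs 12 patients beyond 288, or 20 beyond 280. Those costs hold only while 120 stands. Reaching 80% power on the stated assumptions means 600 in total, 312 more than 288, and nearly all of that increase comes from the per-group figure rather than from dropout.

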**Discussion:**

The SENS-ILIAC trial will give powerful insight into whether the stent choice according to deployment mechanics would impact stent patency, geographic miss, or stent fracture in patients undergoing stent implantation in iliac artery lesions.

**Trial registration:**

National Institutes of Health Clinical Trials Registry (ClinicalTrials.gov identifier: NCT01834495), registration date: May 8, 2012

**Electronic supplementary material:**

The online version of this article (doi:10.1186/s13063-016-1435-9) contains supplementary material, which is available to authorized users.

## Background

For aortoiliac occlusive disease, iliac artery angioplasty with stenting has been a good alternative treatment modality, and endovascular revascularization can be considered without initial extensive conservative treatment [1–5]. The technical and initial clinical success of percutaneous transluminal angioplasty (PTA) of iliac artery stenosis exceeds 90 % in the literature; in addition, the technical success rate of recanalization of obstructive long lesions of iliac artery is 80–85 % with or without additional fibrinolysis [6].

As new types of stents and technical developments have been introduced, more extensive and multifocal iliac lesions have been treated with endovascular procedures [7–11]. Low morbidity and mortality as well as up to 90 % technical success rate guarantee the endovascular-first approach and the patency rates with stenting of iliac arteries compare favorably with those of surgical revascularization. In experienced centers, TransAtlantic Inter-Society Consensus (TASC) type D lesions might be also primarily treated percutaneously [12–14].

In endovascular repair for iliac lesions, unlike the infrapopliteal revascularization strategy, routine stent placement with a PTA strategy has been generally accepted [15]. It was seen in a study of 250 patients undergoing either PTA alone or PTA with provisional stenting that the provisional stenting arm was associated with more than a 2.5-fold reduction (10 vs 4 %) in immediate failures, although long-term results in the two groups were similar [16]. In a meta-analysis of iliac artery intervention studies, the risk of long-term failure was reduced by 39 % after stent placement compared with PTA and the technical success rate was higher after stent placement [7]. A study comparing angioplasty alone with angioplasty plus stenting for complex iliac artery disease showed that cumulative primary patency rates were 78 % at 1 year, with a secondary patency rate more than 80 % at 32 months, with reduction in long-term failure of 39 % when stents were used [17]. In this analysis, stenting improved the 4-year primary patency rates by approximately 10 % for both patients treated for claudication or critical ischemia, and patients treated for iliac stenosis and occlusions.

Stents for iliac artery disease are classified as self-expandable and balloon-expandable according to the mechanics of stent deployment, and as nitinol, stainless steel and others according to stent material. Currently, the choice of balloon- versus self-expandable stent is determined mainly by operator preference. Self-expanding stents are usually made of nitinol, an alloy of nickel and titanium, and stainless steel. Nitinol alloys are most commonly known for their super-elasticity and thermal shape memory [18]. Generally, self-expanding stents have greater elasticity, allowing them to regain their shape after the compression force reduces. Another advantage of self-expanding stents is their higher trackability, meaning they are easier to maneuver through tortuous vessels or pass the aortic bifurcation from the contralateral approach. Balloon-expandable stents are usually made of stainless steel. Balloon-expandable stents are characterized by much greater radial strength compared to self-expanding stents. The main advantages of balloon-expandable stents are the higher radial stiffness and more accurate placement - avoiding geographic miss, which is especially important in aortoiliac bifurcation lesions. Balloon-expandable stents generally have higher radio-opacity, which facilitates accurate placement [19]. In addition, balloon-expandable stents are generally considered more appropriate in rigid and straight lesions [20, 21].

There are some indirect comparative studies that compared balloon-expandable with self-expandable stents [22, 23], and one direct study that compared self-expandable with balloon-expandable stents in a human ex vivo [24]. The outcome of two different self-expanding stents (nitinol versus stainless steel) for the treatment of iliac artery lesions was indirectly compared in a multicenter prospective randomized trial. In the CRISP-US trial [22], the 9-month composite end-point rate was equivalent for the SMART stent versus the Wallstent (6.9 vs. 5.9 %), with low rates of restenosis (3.5 vs. 2.7 %), death (2.0 vs. 0.0 %), and revascularization (2.0 vs. 4.0 %) in both groups. Primary patency at 12 months was 94.7 and 91.1 % with the SMART stent and Wallstent, respectively. The MELODIE study demonstrated that The Express LD balloon-expandable stents were indirectly similar to the Palmatz balloon- expandable stent for primary patency (92.1 % at 6 months and 87.8 % at 2 years) [23]. Grenacher et al. reported that self-expanding stents presented considerably lower radial expansion force and lower degree of precision than balloon-expandable stents in a human cadaver bifurcation model [24]. However, there is no randomized comparative study that compares primary patency rates of the two different types of stent (self-expandable versus balloon-expandable) in patients with iliac artery disease.

Therefore, in this study, we will compare primary patency rates of self-expandable stents and balloon-expandable stents in real-world clinical practice. In addition, we would like to ascertain whether there are differences in safety, including the incidence of geographic miss rate and stent fracture rate, between both stent groups in steno-occlusive lesions, especially for aortoiliac bifurcation lesions.

## Method/design

### Study objectives, hypothesis, and design

The primary purpose of our study is to compare primary patency between self-expandable nitinol stents and balloon-expandable cobalt-chromium stents in real-world clinical practice (COMPLETE-SE™ versus SCUBA™, Medtronic, Minneapolis, MN, USA) in stenotic or occlusive iliac arterial lesions. The secondary purpose is to ascertain whether there is a difference in safety, including the incidence of geographic miss rate and stent fracture rate between both groups in patients undergoing stent implantation in iliac lesions. This is a prospective, randomized, multicenter trial to assess the efficacy and safety of the COMPLETE-SE™ versus the SCUBA™ stent by provisional stenting after balloon angioplasty for steno-occlusive iliac arterial lesions. A description of this manuscript according to the SPIRIT guidelines is presented in Additional file 1

The protocol of the trial has been registered with the National Institutes of Health Clinical Trials Registry (registration number: NCT01834495) and a brief flow chart of the whole study is summarized in Fig. 1.

**Fig. 1 Fig1:**
[figure not shown]
Flow chart of the enrolled patients

### Study population

Patients at least 20 years of age who have moderate or severe intermittent claudication or critical limb ischemia (CLI), Rutherford score of 2 to 6, except for any patient who has undergone or plans to have a major amputation) will be screened for study enrollment. Prior to inclusion, morphological examinations such as computed tomography (CT) and magnetic resonance imaging (MRI) are not necessarily needed. However, we will usually examine the CT angiography prior to the intervention. A patient will be enrolled if they meet all of the inclusion criteria and have none of the exclusion criteria. Inclusion criteria consist of clinical and anatomical criteria.

The clinical inclusion criteria are as indicated below: Symptomatic peripheral artery disease with moderate to severe claudication (Rutherford score of 2 to 3) Chronic CLI with resting ischemic pain (Rutherford score of 4) Chronic CLI with ischemic ulcers (Rutherford score of 5 to 6) Patients must provide written informed consent

The anatomical inclusion criteria are as indicated below: Stenosis of more than 50 % Occlusion of the ipsilateral iliac artery Patent (≤50 % stenosis) ipsilateral femoropopliteal artery, or concomitantly treatable ipsilateral femoropopliteal lesions (≤30 % residual stenosis), and at least one patent (less than 50 % stenosis) tibioperoneal run-off vessel. We will not exclude patients who have undergone femoral endareterectomy. If inflow and outflow disease can be treated (except by bypass surgery), we will enroll these patients

Exclusion criteria include the following:Failure to provide written informed consentA history of major bleeding within the prior 2 monthsKnown hypersensitivity or contraindication to any of the following medications: heparin, aspirin, clopidogrel, cilostazol, or contrast agentAcute limb ischemiaPrevious bypass surgery or stenting of the ipsilateral iliac arteryUntreated inflow disease of the distal aorta (>50 % stenosis or occlusion)Patients who have undergone major amputation (amputation of above the ankle) or major amputation is planned or requiredPatients with a life expectancy of less than 1 year due to comorbidities

### Randomization and interventions

Prior to the endovascular intervention, informed consent (see Additional file 2) will be obtained from all participants by investigators. Aspirin and clopidogrel will be administered at least 12 hours before the procedure. Prior to the intervention, 70 to 100 units/kg of unfractionated heparin will be administered. Endovascular interventions will be carried out percutaneously, by placing a 6–8Fr sheath at the femoral artery via an antegrade approach or a contralateral crossover technique. In selected cases, a retrograde approach (from the distal superficial femoral artery (SFA), popliteal artery, or pedal arteries) and/or brachial approach will be allowed. Diagnostic angiography will be performed in two different views at least 30 to 45° apart to evaluate the structure of the target lesion. Femoropopliteal and tibial arteries will be visually checked for the presence of distal lesions. To document the precise location of the lesion and the site of the intervention, we will recommend the use of a ruler. In cases of total occlusion, both intraluminal and subintimal methods of recanalization will be allowed. During the procedure, the use of other special devices will be allowed; for example reentry devices OUTBACK™ catheters (Cordis Corp., Miami Lakes, FL, USA) and Offroad catheters (Boston Scientific, Natick, MA, USA), chronic total occlusion (CTO) devices Frontrunner (Cordis Corp., Miami Lakes, FL, USA) and Truepath (Boston Scientific, Natick, MA, USA), and atherectomy devices such as SilverHawk™ and TurboHawk™ (Covidien, Plymouth, MN, USA). After the successful passage of the guidewire, predilation of the target lesion with an optimally sized balloon will be performed prior to stent implantation. Recommended minimal balloon dilation time is 120 seconds. Then, if there is a residual pressure gradient of ≥10 mmHg, residual stenosis of ≥30 %, or flow-limiting dissection, the balloon angioplasty results will be considered as suboptimal results. Subsequently, web-based randomization for stent selection will be performed. Patients will be randomly allocated to one of two groups, the balloon-expandable or self-expandable stent group, according to the stent deployment method. Random allocation of the patients will be performed via a web-based computerized program separately managed at the Cardiovascular Intervention Research Institute (CIRI), Korea University Guro Hospital, Seoul, Republic of Korea. Patients will be randomized in a 1:1 manner according to two different stents (SCUBA™ versus COMPLETE-SE™). The stents will be implanted to extend 10 mm proximally and distally from the margins of the target lesion with luminal narrowing of ≥50 %. A proper stent size will be selected after review of the baseline angiography results. If the stent is randomized to the COMPLETE-SE™, a stent with a diameter 1 to 2 mm larger than that of the true vessel lumen will be selected. However, if the stent is randomized to the SCUBA™ stent, a stent of equal size to the reference vessel diameter will be selected to prevent iliac artery injury. Spot stenting or full lesion coverage will be decided at the physician’s discretion. When multiple stents are required, the margins of the stents should be overlapped by at least 10 mm. Adjuvant postdilation after the stenting will be performed strictly within the stented segment, with up to 10 % oversizing of the postdilation balloon.

The self-expandable COMPLETE-SE™ stent has three distinct crown configurations, and an alternating connection pattern minimizes crown-to-crown interaction and provides optimal flexibility, foreshortening, and lesion coverage for each stent size. The triaxial deployment design includes an inner shaft, a retractable sheath, and a stabilizing sheath, which reduces friction and allows the retractable sheath to move back freely. This decreases the amount of force required to deploy the stent, making deployment easy and accurate. Diameter and length of self-expandable COMPLETE-SE™ stents are 5–10 mm and 20, 40, 60, 80, 100, 120, and 150 mm, respectively. Balloon-expandable SCUBA stents are composed of thin cobalt-chromium struts, unlike other stainless steel stents, and have a closed-cell design for tight scaffolding and appropriate radial strength in iliac lesions. Diameter and length of balloon-expandable SCUBA™ stents are 6–10 mm and 20, 30, 40, and 60 mm, respectively. The entire stent size (the COMPLETE-SE™ and SCUBA™ stent) is now 6-Fr sheath compatible. We will use either a 0.035” or 0.018” wire system and implant either a SCUBA™ or COMPLETE-SE™ stent. All ipsilateral femoropopliteal arterial lesions should be treated with angioplasty and/or stenting concomitantly and residual stenosis should be less than 50 %. Treatment of tibioperoneal lesions is recommended only in cases of CLI. There should exist at least one patent (<50 % stenosis) tibioperoneal run-off vessel with good antegrade flow. A final angiography will be performed after the intervention in both groups, with the use of the same angles and magnifications used at the baseline angiograms. Simultaneously, reference vessel diameter (RVD), minimal luminal diameter (MLD), percent diameter stenosis, and acute gain should be measured. The RVD will be obtained from averaging 5-mm segments proximal and distal to the lesion. Technical success will be defined as successful access, deployment of the stent, and less than 30 % diameter residual stenosis after the revascularization. For postprocedural medication, aspirin 100 mg and clopidogrel 75 mg will be administered once daily for at least 12 months. Cilostazol would be permitted as the third antiplatelet at the physician’s discretion. After enrollment and index procedure, clinical follow-up will be planned at 1, 6, and 12 months to evaluate clinical outcomes and ankle-brachial index (ABI) score. In addition, a follow-up catheter angiography, CT angiography, or duplex ultrasound will be recommended to all patients at 12 months, according to local clinical practice. The investigators will be urged to follow up on patients, either by office visits or by telephone contacts, as necessary. Patient adherence to the study drug and side effects will be checked and monitored at every outpatient visit. The decision of drug discontinuation will be discussed and checked at the physician’s recommendation.

Participants have the right to withdraw from the study at any time for any reason. The principal investigator also has the right to withdraw patients from the study in the event of protocol violations, administrative reasons, or other reasons, e.g., the participant is no longer being treated at a hospital included in the study. It is understood by all concerned that an excessive rate of withdrawals can render the study uninterpretable; therefore, unnecessary withdrawal of patients should be avoided.

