### Statistical analysis

The IBM SPSS 20.0 (IBM Corp., Armonk, NY, USA) statistics program will be used for all analysis. Categorical variables will be expressed as delivery rate when comparing baseline features between the SCUBA™ and COMPLETE-SE™ stent groups and for categorical variables, comparisons between groups will use the chi-square or Fisher’s exact test. Continuous variables will be expressed as mean ± standard deviation, and for continuous variables, comparisons between groups will use the Student’s *t* test. The primary and secondary end points will be analyzed using both intention-to-treat analysis (all subjects assigned to a treatment group) and per protocol analysis (only subjects who completed the treatment protocol). Noninferiority will be considered proven if conclusions drawn from the intention-to-treat and per protocol analyses are consistent. Balloon-expandable stent patency will be judged as noninferior to that of the self-expandable stent when the lower limit of the 95 % CI of the difference between the proportions of patent patients at 1 year in both groups is higher than -δ = −10 % At the end of the 12 months, cumulative restenosis rates will be calculated. For a secondary end point, we will summarize with descriptive statistics and compare between treatment groups using the Student’s *t* test, chi-square test, or Fisher’s exact test. Also, clinical outcomes such as revascularization of the target vessel, death, major cardiovascular events including myocardial infarction and cerebral infarction, and limb salvage rates will be analyzed using Kaplan-Meier survival estimates and a comparison of the groups will be performed using the log-rank test. A *P* value <0.05 will be considered to be statistically significant. In order to evaluate the risk factors for recurrence, defined as restenosis or total occlusion, univariate and multivariate logistic regression analysis will be performed. The present research has concluded that there will be a very low chance of missing data to cause bias, and therefore, missing data for the major end points will be excluded from the analysis data.

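### The principal investigator may withdraw randomised patients from the study for protocol violations, administrative reasons or care elsewhere; with missing end points excluded, such patients can drop out of both the ITT and the per-protocol result

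*Protocol article*

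**What the plan says.** The withdrawal paragraph closes the section Randomization and interventions of the protocol article. After the patient's own right to leave, it adds that the principal investigator may "withdraw patients from the study in the event of protocol violations, administrative reasons, or other reasons, e.g., the participant is no longer being treated at" any participating hospital. The only restraint is advisory: the paragraph warns that "an excessive rate of withdrawals can render the study uninterpretable; therefore, unnecessary withdrawal of patients should be avoided".

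Three other statements bear on this.

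- **Timing of allocation (same section).** Randomisation takes place during the procedure, after a suboptimal balloon result: "Subsequently, web-based randomization for stent selection will be performed". The sizing rule then differs by arm, so the operator knows which stent was allocated.
- **Follow-up (same section).** "The investigators will be urged to follow up on patients, either by office visits or by telephone contacts, as necessary".
- **Analysis sets (Statistical analysis).** The end points are analysed by "intention-to-treat analysis (all subjects assigned to a treatment group) and per protocol analysis (only subjects who completed the treatment protocol"). Noninferiority counts as proven if the two analyses agree. The same section says that missing data on the major end points are left out of the analysis.

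**The concern.** A noninferiority trial with an evident allocation needs every randomised patient followed to the primary end point whatever happens after allocation. A protocol violation is normally a reason to leave the per-protocol set. Here it can end a patient's participation in the study, as can administrative reasons, other reasons, or a move to a hospital outside the trial.

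These grounds could be related to outcome. A patient who has a reintervention, bypass or amputation at an outside hospital could fall under the transfer-of-care example. Implantation of the non-allocated stent could be treated as a protocol violation. If such patients leave before 12 months without a patency reading, the estimated difference in patency can be biased. In the Kaplan-Meier analyses of target vessel revascularisation, death, major cardiovascular events and limb salvage, they would be censored at a time that may depend on prognosis.

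**Working it through.** **1. How the clauses combine.**

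- The withdrawal paragraph allows a randomised patient to be taken out of the study before 12 months.
- Such a patient may then have no 12-month patency result.
- The Statistical analysis section excludes missing major end points.
- The patient is therefore absent from the ITT estimate, although ITT is defined as all subjects assigned, and also from the per-protocol estimate.
- The agreement requirement cannot detect this, because both analyses lack the same patient.

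The effect needs both clauses. Withdrawal creates the gap, and the exclusion rule carries it into the ITT result.

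**2. Inputs for an illustration.** The withdrawal clause states no figure to reproduce.

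- From Sample size calculation: margin 10 points; one-sided 2.5%; 120 evaluable per group; 288 in total, that is 2 x 120 x 1.2, or 144 per arm. (The abstract says 280; 144 is used here. Whether 120 follows from the stated rates is a separate question and does not affect this point.)
- From the same section: 90% patency for COMPLETE-SE.
- Assumed: true SCUBA patency of 80%, exactly on the margin, so that noninferiority should be declared 2.5% of the time. The plan expects 88%.
- Assumed: the numbers of failures withdrawn and dropped as missing.

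**3. Difference after withdrawal.** Expected patent patients are 0.80 x 144 = 115.2 (SCUBA) and 0.90 x 144 = 129.6 (COMPLETE-SE). Withdrawing a SCUBA failures and b COMPLETE-SE failures gives

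difference = 115.2/(144 - a) - 129.6/(144 - b).

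| SCUBA failures withdrawn | COMPLETE-SE failures withdrawn | Difference (points) |
|---|---|---|
| 0 | 0 | -10.0 |
| 5 | 1 | 115.2/139 - 129.6/143 = -7.75 |
| 7 | 1 | 115.2/137 - 129.6/143 = -6.54 |
| 3 | 3 | 115.2/141 - 129.6/141 = -10.2 |
| 1 | 5 | 115.2/143 - 129.6/139 = -12.7 |

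Equal proportions behave differently from equal counts. Withdrawing 20% of the failures in each arm (5.8 and 2.9 patients) gives 0.833 - 0.918 = -8.5 points.

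**4. False noninferiority rate.** The chance that the lower 95% limit lies above -10 is Φ[(difference + 10)/SE - 1.96].

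- At 120 per arm, SE = √(0.80 x 0.20/120 + 0.90 x 0.10/120) = 4.56 points. With no shift the rate is Φ(-1.96) = 2.5%. For the 5:1 split, Φ(2.25/4.56 - 1.96) = Φ(-1.47), about 7%.
- With the 139 and 143 patients actually left, and the shifted rates, SE = 4.02 points and Φ(2.25/4.02 - 1.96) = Φ(-1.40), about 8%.
- With 20% of failures lost in each arm, the rate is about 6%.

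**5. Would such losses stand out?** Six withdrawals are 6/288 = 2% of the trial. The planned allowance is 144 - 120 = 24 per arm. The failures expected under the plan's own rates are 0.10 x 144 = 14.4 and 0.12 x 144 = 17.3 per arm. Withdrawals of this size would sit well within the planned dropout.

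**The case against.** The clause gives a right and imposes no duty. It names neither failed nor switched patients, and it says that "unnecessary withdrawal of patients should be avoided". A reader might infer that it removes failures and switches from the trial. The text does not say so; it only makes this possible.

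A reader might also count an additional stent as a protocol violation. The document points the other way: Randomization and interventions provides for multiple stents, and additional stent deployment is recorded within the geographic-miss end point.

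The article does not say that data collection stops at withdrawal. That is the natural meaning of leaving the study, but it is an inference, and a fuller protocol might keep vital status or earlier events.

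The right to withdraw does not contradict the follow-up sentence or the ITT definition taken alone, since a withdrawn patient is still an assigned patient. Much of the effect comes from the rule on missing end points, and counting withdrawn patients as failures, or a tipping-point analysis, could bound it.

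Finally, the 5:1 and 7:1 splits are assumptions, and other splits move the difference against noninferiority.

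All of this limits the claim. What remains is that a stated clause lets events after allocation end follow-up at an investigator's discretion, and the stated analysis then excludes those whose end point is missing. Sensitivity analyses can bound a loss of this kind but cannot restore readings that were never taken.

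**Conclusion.** The point holds as a weakness in a stated rule that should be corrected; it does not show that bias will occur. It rests on three things: withdrawal is from the study and can follow randomisation; the allocation can be known to the person deciding; and missing major end points are excluded, so a withdrawn patient can be absent from both analyses. It also assumes that a withdrawn patient has no 12-month patency result.

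Neither the direction nor the size of any bias can be derived from the document. The rise in false noninferiority from 2.5% to about 7-8% belongs to one assumed split on an assumed boundary truth. Reading it as an estimate for this trial, or as evidence that the clause favours SCUBA, would go further than the text allows.

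**What to change.** In the withdrawal paragraph, remove protocol violation, administrative reasons, the open category of other reasons, and transfer of care as grounds for ending study follow-up. State that:

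- only the patient's withdrawal of consent ends follow-up;
- a protocol violation affects per-protocol membership only;
- all other randomised patients, including any who received the non-allocated stent or moved to another hospital, are followed to 12 months;
- 12-month imaging is sought wherever the patient is treated; where it cannot be had, telephone contact and, where consent allows, outside records are used for death, reintervention, amputation, myocardial infarction and stroke.

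The cost is a wording amendment and some added follow-up work, partly through the telephone route that the article already provides. No extra patients are needed. The trial was still recruiting when the article appeared, so an amendment at that stage could still prevent losses; access to outside records may need consent cover that is not visible here.

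The change does not solve everything. Telephone contact and records do not supply a patency reading, so some primary end points will still be missing, and the exclusion rule in Statistical analysis has to be dealt with separately.
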